#### **6.2.2 Trial design rationale**

##### Rationale for dose escalation via dosing duration

We have elected to escalate the exposure level based on the duration of dosing (in Segment A followed by Segment B) rather than by altering the concentration of antibody per film, for several reasons. As a practical matter, the expense of manufacturing and characterizing films with three different concentrations of the two MAbs is resource intensive and beyond the means of our program. Second, the loading level of 10 mg of each of the two antibodies is very near the practical loading limit, and we are unable to increase the dose substantially without enlarging the film, or inserting a second film, both of which may result in excessive time require for hydration of the film in the vagina.

##### Rationale for daily dosing in Segment B

In addition to providing a dose frequency escalation and thus mimicking intensive precoital use of the MB66 film, the seven sequential doses given in Segment B also serve to explore an alternative dosing regimen, namely, daily, non-coital use, including assessments of the effect of repeated dosing on antibody pharmacokinetics and distribution.

### Rationale for vaginal sampling methods and timing

**Tear Flo sampling:** We have chosen the Tear Flo filter paper (previously marketed as Sno Strip) sampling method (Quesnel et al., 1997; John GC et al., 2001; Sherlock et al., 2006; Bennetto-Hood et al., 2009) for our vaginal PK measurements instead of cervicovaginal lavage (CVL) or higher capacity absorptive sampling devices (swabs or Weck-Cel sponges) based on the following rationale: First, our goal is to sample multiple discrete locations in order to observe the extent of distribution of the MABs in the vagina as a function of time since dosing, and to test the hypothesis that repeated daily doses will improve the extent of MAB distribution over that observed after a single dose. To this end we want to obtain a limited sample volume, taken over multiple limited sampling areas to avoid depletion of MAB by the sampling method (as would occur with CVL or larger capacity sponge sampling devices), thus minimally perturbing residual vaginal antibody and allowing for repeated sampling of the same individual. Second, unlike CVL sampling the Tear Flo method allows for a close estimate of the sampled volume and thus the subsequent dilution factor. Third, Tear Flo filter paper strips have been widely used for vaginal research, including sampling of immunoglobulins, antiretrovirals, and viral load measurements (Quesnel, 1997; Sherlock, 2006; Bennetto-Hood, 2009; John, 2001). We are aware that despite use of Tear Flo sampling, some depletion of vaginal antibody levels will occur due to sequential sampling of the same individual, but expect this to be sufficiently modest in effect to provide an adequate preliminary picture of antibody persistence after dosing in this Pre-Phase I study. Tear Flo samples will be tested for VRC01-N and HSV8-N antibody levels (in validated ELISA assays using Intertek Pharmaceutical Services SOPs to GLP standards). (Intertek Pharmaceutical Services [name]).

**Effect of sampling procedures on film retention and antibody levels:** Other aspects of our procedure are recognized to also have some potential for depletion of vaginal mAb levels. The speculum required to obtain localized samples from multiple sites has the potential to remove antibody or partially hydrated film. We will attempt to minimize this by removing adherent film or fluid from the speculum with a wooden tongue depressor and tip the speculum to maximize vaginal retention of fluid during speculum withdrawal.

**CVL sampling and timing:** CVL sampling is required for assessments for which Tear Flo sampling gives inadequate volumes, namely for viral neutralization studies and immune mediators. CVL sampling will be delayed until after Tear Flo sampling has been completed at the 24 h post dosing time point, a time when data adequate to calculate the vaginal retention kinetics from the 1, 4, and 24 hours Tear Flo sampling without interference from CVL sampling, has already been obtained. An estimate of the amount of film inadvertently removed, if any, will be recorded.

### Rationale for non-exclusion of HSV seropositives

Participants will not be pre-screened for HSV-2 (or HSV-1) antibodies (to detect for infection with HSV-2 or HSV-1). The resources available for screening/recruitment in this Pre-Phase I study with IPCP funding are not adequate to allow screening out both HSV-2 and HSV-1 seropositive individuals, together estimated to be approximately 50% of the expected otherwise eligible study candidates based on both national surveys and on experience at studies based at

Miriam Hospital. Screening out only HSV-2 positive women will not be helpful since both anti-HSV-1 and HSV-2 endogenous antibodies will both bind in the ELISA assay. We strongly expect both VRC01-N (anti-HIV) and HSV8-N (anti-HSV) antibodies to have very similar absorption, so data on VRC01-N will provide strong preliminary evidence of the level of systemic exposure to both antibodies. Moreover, approximately half the participants are expected to be HSV double seronegative (negative for both serotypes) even without screening, and will contribute substantial direct data on HSV8-N absorption. Regarding vaginal samples, vaginal levels of anti-HSV antibody are very low (generally sub-microgram/mL) even in HSV seropositive individuals (Wang, 2014). Considering these low baseline values, we therefore expect little difficulty assessing the vaginal PK at levels clinically relevant to our criteria for likely protection (~100 ug/mL), even in HSV seropositive participants.

#### Rationale for choice of HIV tests in a study of VRC01-N

An anti-HIV-1 gp120 antibody (VRC01-N) is being vaginally applied in this study. Although the bioavailability of vaginally applied antibodies has been found to be low (see Section 6.1.3), there is a theoretical risk that small amounts of antibody may be absorbed and might be sufficient to cause a false positive HIV antibody test. For this reason we have chosen to use the OraQuick Rapid HIV 1/2 test for the HIV antibody testing done in this study (at baseline and followup) because the test does not include an HIV gp120 target. Although not being used in the present study, there are some HIV antibody tests that do use HIV gp120 target antigen. There is a theoretical risk of false positive results with HIV antibody tests that do contain gp120. However, even these tests appear not to react with VRC01 antibody. The University of Washington Virology Specialty Laboratory (UW-VSL, [name]), in conjunction with the HVTN and the VRC/NIH, has tested HIV uninfected human plasma samples spiked with VRC01 at 200 mcg/mL, 50 mcg/mL, 12.5 mcg/mL, 3.1 mcg/mL and 0.8 mcg/mL, and did not observe positive test results in several standard antibody-based HIV-1/2 diagnostic tests used in the US (personal communication [name], HVTN/Fred Hutchinson Cancer Research Center, Seattle, WA, USA). Additional testing is being done in those and other trials of systemically administered VRC01, and we will rely on information from those trials rather than make further assessments of possible interactions with VRC01-N and such HIV blood tests during the present pre-Phase I study.

### **6.3 STUDY HYPOTHESES**

The study will test the following hypotheses:

1. That the MB66 film will be safe as compared to placebo vehicle only film;
2. That the MB66 film will show adequate dissolution, distribution, and residence time for pre-coital use;
3. That antibody distribution will be enhanced and residence time will be lengthened by daily administration of film compared to a single film administration.

## **7. STUDY OBJECTIVES**

### **7.1 PRIMARY OBJECTIVE**

To evaluate the safety of the MB66 film

### **7.2 SECONDARY OBJECTIVES**

To measure pharmacokinetic parameters including:

- The rate of MB66 film dissolution
- The vaginal concentrations of the MB66 antibodies
- The degree of systemic absorption of the MB66 antibodies

### **7.3 EXPLORATORY OBJECTIVES**

- To assess the antiviral effect of the MB66 antibodies *ex vivo* in cervicovaginal lavage fluid from participants after dosing with MB66 film
- To compare the effects of MB66 and placebo films on the cervicovaginal microbial environment using pH, Nugent score, and bacterial ribosomal DNA PCR
- To compare the effect of MB66 and placebo films on cervicovaginal immune mediators by Luminex and ELISA assays
- To assess the acceptability of the MB66 vaginal film after 7 days of use

## **8. STUDY DESIGN**

### **8.1 OVERVIEW**

This is a single center, Pre-Phase 1, randomized, single blind, placebo-controlled, two-segment study to assess the safety of the MB66 vaginal film. After appropriate screening, approximately 43 healthy women will be enrolled for a target evaluable population of 38 healthy, HIV uninfected women 18-45 years of age.

The study will be divided into two sequential Segments. The first, Segment A, is a single-arm, single-dose, open label design. The 8 participants will receive a single dose of one full MB66 film. After dosing, subjects will be asked to maintain sexual abstinence and will be evaluated in person on Day 1 (24-hours post MB66 administration), by telephone on Day 3 or 4 and in person on the Day 6-10 Exit Visit, after which subjects will be allowed to resume sexual activity with study-provided condoms until three weeks after last exposure to film (to avoid male exposure to residual drug product). A placebo arm was not included in Segment A, because the very low risk of toxicity of the placebo film makes it unlikely that toxicity observed in Segment A would be wrongly attributed to the active agents (mAbs) in the MB66 film when it was instead due to the vehicle. This conclusion is based on the known tolerance of the very similar vehicle used in a commercial PVA-based vaginal film (VCF), and the absence of toxicity of the MB66 placebo

film in the very sensitive rabbit model after substantially higher dosing intensity and duration (see Section 6.1.3). [Figure 1](#) (Section 5) shows a diagram of the Segment A study schema.

Completion of Segment A and a safety review of Segment A adverse events will trigger the initiation of Segment B ([Figure 2](#), Section 5), a repeat dose, randomized, two arm, single-blind, placebo-controlled design. Subjects will be randomized 1:1 into two groups (15 evaluable subjects per group) and be treated once daily with either 1 MB66 film or 1 vehicle control placebo film for seven days. For five days before, and for 7 days after the dosing period, subjects will be asked to maintain a period of sexual abstinence. Subjects will be evaluated in person on Day 0 (at 1 and 4 hours post MB66 in-clinic dosing), again on Day 1 (24 hr post dosing), by telephone on Day 3-4, and evaluated again in person on Day 7-8, after which, subjects will be allowed to resume sexual activity with condoms required until three weeks after last film insertion. Subjects will be evaluated a last time on the Day 12-16 Exit Visit.

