## **8.5 EXPECTED DURATION OF PARTICIPATION**

The duration of study participation per woman is expected to be approximately 5-9 weeks, including the screening period. Participation from enrollment to Exit Visit is 1 week for Segment A and 2 weeks for Segment B, plus an additional 2 weeks of post exit mandated condom use.

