## **9.2 INCLUSION CRITERIA**

Women must meet all of the following criteria to be eligible for inclusion in the study:

- 1) Age 18 through 45 years (inclusive) at screening
- 2) Able and willing to provide written informed consent to be screened for and enrolled in the study
- 3) Able and willing to provide adequate locator information at screening
- 4) HIV-uninfected based on testing performed by study staff at screening (per algorithm in [Appendix 2](#))
- 5) In general good health as determined by the site clinician
- 6) Agree to abstain from any vaginal insertions, including products, douches, devices such as sex toys, or penile or oral intercourse from 5 days prior to Visit 2 (Enrollment Visit) until

the final Study Visit (one week after last dose of study film). Only tampons during menses and clinically indicated speculum exams are allowed.

- 7) Agree to use condoms provided by the study staff from one week after last use of study film until three weeks after last use of study film
- 8) Willingness to undergo all study-related assessments and follow all study-related procedures
- 9) Be currently using an effective method of contraception at enrollment (used continuously and with good compliance for the past 60 days as determined by participant self-report) with plans to continue use throughout the study period. Acceptable methods include any hormonal method (except vaginal ring); intrauterine device (IUD) inserted at least 90 days prior to enrollment; female sterilization; abstinent from sexual activity with male partner for the past 60 days; sexual activity with vasectomized partner; engages in sex exclusively with women.
- 10) For participants 21 and older, a Pap result in the 36 calendar months prior to the Enrollment Visit consistent with Grade 0 according to the Female Genital Grading Table for Use in Microbicide Studies Addendum 1 to the DAIDS Table for Grading Adult and Pediatric Adverse Events, (see Reference 40) satisfactory evaluation with no treatment required of non-Grade 0 Pap result per American Society for Colposcopy and Cervical Pathology (ASCCP) guidelines or per local standard of care, within the last 36 calendar months prior to enrollment.  
  
*Note: For participants aged 18-21, a Grade-0 or adequately evaluated abnormal Pap smear is not required as the American Society for Colposcopy and Cervical Pathology recommends initiating screening at age 21.*

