**Table 13: Segment B, Visit 4 Procedures (Follow-up at Day 7)**

| Component                | Procedure/Analysis                                                                                                                                                                                                                                            |
|---------------------------------|----------------------------------------------------------------------------------------------------------------------------------------------------------------------------------------------------------------------------------------------------------------------|
| Administrative/Interview | Visit 4 Interview
Adverse event collection
Update concomitant medication log
Receive returned unused films
HIV pre- and post-test counseling
Acceptability interview (CASI)
Abstinence counseling
Schedule Visit 5 appointment
Reimbursement |
| Urine                    | Dipstick Urinalysis
Pregnancy test (HCG)
NAAT for chlamydia, gonorrhea, and trichomonas Δ                                                                                                                                                           |

| Component                            | Procedure/Analysis                                                                                                                                                                                                                                                                                                                                                |
|--------------------------------------|-------------------------------------------------------------------------------------------------------------------------------------------------------------------------------------------------------------------------------------------------------------------------------------------------------------------------------------------------------------------|
| Blood                         | Serum for study product MAb levels
Complete blood count Δ
AST, ALT, Creatinine Δ
Syphilis screen (RPR) Δ
Confirmatory HIV testing Δ                                                                                                                                                                       |

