### **11.2.2 Participants Who Become Pregnant**

Participants will be counseled to be sexually abstinent from five days prior to enrollment to seven days after their last dose of study film, and to use condoms during vaginal intercourse until three weeks after their final MB66 administration, and to continue their requirement for use of an effective contraceptive regimen (see Section 9.2). Urine pregnancy tests will be done on Screening, Enrollment and Exit Visits. Participants with positive pregnancy tests at Screening or Enrollment Visits will not be enrolled. Participants with a positive pregnancy test at the Exit Visit will be referred for obstetrical care. Women who become pregnant during the study period after randomization and exposure to study product will not be excluded from analysis. The study team will request that the participant signs a medical release form, so that information about the status of the pregnancy and health of the newborn can be included in future reports about the study product. Every effort will be made to maintain periodic contact with the participant after study termination until the completion of the pregnancy in order to determine the pregnancy outcome, and to obtain records from the facility at which the outcome occurred.

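### Section 8.1 contradicts itself on Segment B abstinence: it asks for 7 days after dosing, then allows sex with condoms about 1 day after the last film and 4 to 9 days before the exit visit

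*Protocol*

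**What the plan says.** Two statements in the Segment B paragraph of Section 8.1 of the protocol give different end points for abstinence. The first reads: "For five days before, and for 7 days after the dosing period, subjects will be asked to maintain a period of sexual abstinence". The next sentence lists the in-person visits and says women are "evaluated again in person on Day 7-8, after which, subjects will be allowed to resume sexual activity with condoms required", with the condom requirement running to three weeks after the last film.

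The rest of the protocol bears on which is meant:

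- Section 8.1, Segment A, ties release to the "Exit Visit, after which subjects will be allowed to resume sexual activity with study-provided condoms".
- Inclusion criterion 6 (Section 9.2) bars vaginal insertions and intercourse until "the final Study Visit (one week after last dose of study film). Only tampons during menses and clinically indicated speculum exams are allowed".
- Inclusion criterion 7: "Agree to use condoms provided by the study staff from one week after last use of study film", continuing to three weeks after the last film.
- Section 11.2.2 has women counseled to be "sexually abstinent from five days prior to enrollment to seven days after their last dose of study film".
- Section 8.5 gives two weeks from enrollment to exit for Segment B, "plus an additional 2 weeks of post exit mandated condom use".
- Table 13 (Visit 4) lists "Abstinence counseling" and no condom counseling or distribution. Condom counseling and distribution first appear at Visit 5, in Tables 14 and 20.
- Section 11.1.2.2 ends abstinence at Visit 4, yet describes that point as roughly two weeks after enrollment and one week after the last film, which is Visit 5.

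**The concern.** Both statements in 8.1 cannot be followed. A woman released at Visit 4 has not completed the 7 days that the preceding sentence requires.

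Two things depend on the rule. The first is partner protection. Section 17.2.1 leaves male partners unconsented and unmonitored, partly because the abstinence and condom rules are expected to keep them from exposure. Section 8.1 itself, for Segment A, gives avoidance of male exposure to residual product as the purpose of the condom period.

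The second is the interpretation of Visit 5. That visit includes a pelvic safety exam, adverse event collection, vaginal pH, Gram stain, a microbiome swab, Tear Flo sampling and lavage (Section 11.1.2.7, Table 14). Intercourse in the preceding days would add a competing explanation for genital findings, which inclusion criterion 6 keeps out. By Section 14.5, staff at the site cannot reliably be blinded to assignment when they judge such findings.

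**Working it through.** The protocol states no figure for the gap, so there is none to reproduce. The check is day arithmetic on the stated schedule.

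**Inputs**

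- Last film: Day 6 on the normal schedule (Protocol Summary: Day 0 in clinic, Days 1-6 at home), or Day 7 if Visit 4 moves to Day 8 (Section 10.3).
- Visit 4: Day 7 or Day 8, timed at 24 (+/-4) hours after the last dose (Section 11.1.2.6).
- Visit 5: Day 12 to 16, target Day 14 (Section 11.1.2.7).
- Required abstinence after the last film: 7 days (8.1 first statement, 11.2.2).

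**Release under the 8.1 permission, for women who dosed the day before Visit 4**

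- Days since last film: 7 - 6 = 1, or 8 - 7 = 1.
- Seven-day mark: 6 + 7 = Day 13, or 7 + 7 = Day 14.
- Days early: 13 - 7 = 6, or 14 - 8 = 6.
- Days before Visit 5 and the first listed condom distribution: shortest 12 - 8 = 4, longest 16 - 7 = 9, target dates 14 - 7 = 7.

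**Number of women who could be affected**

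About 43 are enrolled to reach 38 evaluable (Section 14.2), which allows 43 - 38 = 5 replacements. If all five fall in Segment B, enrollment there is 43 - 8 = 35. Enrolled women are the right count because the instruction reaches women whether or not they later prove evaluable.

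**Is naming the Exit Visit enough?**

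The table sets the two possible dosing schedules against the five possible Visit 5 days.

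| Visit 5 day | Days since last film (Day 6 / Day 7) | Later of Visit 5 and seven-day mark (Day 6 / Day 7) |
|---|---|---|
| 12 | 6 / 5 | 13 / 14 |
| 13 | 7 / 6 | 13 / 14 |
| 14 | 8 / 7 | 14 / 14 |
| 15 | 9 / 8 | 15 / 15 |
| 16 | 10 / 9 | 16 / 16 |

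Release at Visit 5 alone falls 1 or 2 days short of seven in 3 of the 10 combinations. Release at seven days alone, as 11.2.2 reads, can come up to 16 - 13 = 3 days before Visit 5. Requiring both gives Day 13 to 16 and satisfies inclusion criteria 6 and 7 in all ten. The condom requirement then ends at 6 + 21 = Day 27 or 7 + 21 = Day 28, as 8.1 already intends.

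**The case against.** The strongest reply is that the wrong clause sits in an overview, while nearly all the working text is right. Staff using the Visit 4 table would counsel abstinence and hand out no condoms. There is one site, and the consent form is not available here, so nothing shows that women were told the 8.1 version. This stands as a limit on likelihood: harm requires the site to follow 8.1 over inclusion criterion 6. It does not excuse an explicit permission in the design section that contradicts the sentence before it, especially as 11.1.2.2, which sets out what women must agree to at screening, carries a related visit-number error.

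Four stronger readings are tempting and should be set aside.

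- A reader might infer that partners are left unprotected. The same clause in 8.1 keeps condoms mandatory. What is lost is the abstinence margin and the study's own condom supply.
- A reader might infer that the primary analysis or the microflora endpoints are compromised. The 30% rule and evaluability do not change, and the pH and Nugent definitions use Visit 4 (Sections 14.4.3 and 14.7.4), before any early release. At Visit 5 the investigator can weigh intercourse when judging relatedness (Section 12.1.1). Some confounding of Visit 5 findings remains possible, but the documents give no basis for sizing it.
- A reader might cap the exposure at the 30 evaluable women. Enrolled women are the relevant count, as shown above.
- A reader might see a further contradiction in Section 10.9, which exempts female condoms from the products to avoid during participation. Section 8.5 counts the post-exit condom phase as participation, so 10.9 has a consistent reading.

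It can also be said that the extra seven-day condition only tidies ordinary visit windows, since inclusion criterion 6 treats the final visit and one week after the last dose as the same time. The differences are indeed only 1 to 3 days. The condition is worth adding because the sentence must be rewritten anyway.

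**Conclusion.** The concern holds as an internal drafting inconsistency in an operative rule; the intended design is clear from the rest of the protocol. As written, 8.1 releases Segment B women about 1 day after the last film, 6 days before the required point and 4 to 9 days before the visit where condom distribution is first listed. It could reach any enrolled Segment B woman, up to about 35. That ceiling assumes that every replacement falls in Segment B. The number actually exposed would be smaller, since inclusion criterion 9 also admits women without male partners.

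The 1-day and 6-day figures assume film use on the day before Visit 4. They do not apply to women who stopped product earlier. The consequence also depends on the site acting on 8.1, which the documents neither show nor rule out. It should be corrected, and the correction touches no analysis.

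**What to change.** In Section 8.1, delete the Day 7-8 permission and close the Segment B paragraph along these lines: *A final evaluation takes place at the Exit Visit (Visit 5, Day 12-16). Sexual activity with study-provided condoms may resume after the Exit Visit and no earlier than seven days after the last film; condoms are required until three weeks after the last film.* In Section 11.1.2.2, change Visit 4 to Visit 5. Check that the Segment B consent and counseling scripts say the same.

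Inclusion criteria 6 and 7 can stay as they are. Aligning the end date in 11.2.2, or limiting the female-condom exemption in 10.9 to the period after abstinence, would be an optional clarification and is not part of the error.

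The cost is wording in two places plus the document check, with no added visits, samples or analyses.
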